## Abstract

**Background:**

Kids - 'Go for your life' (K-GFYL) is an award-based health promotion program being implemented across Victoria, Australia. The program aims to reduce the risk of childhood obesity by improving the socio-cultural, policy and physical environments in children's care and educational settings. Membership of the K-GFYL program is open to all primary and pre-schools and early childhood services across the State. Once in the program, member schools and services are centrally supported to undertake the health promotion (intervention) activities. Once the K-GFYL program 'criteria' are reached the school/service is assessed and 'awarded'. This paper describes the design of the evaluation of the statewide K-GFYL intervention program.

**Methods/Design:**

The evaluation is mixed method and cross sectional and aims to:

1) Determine if K-GFYL award status is associated with more health promoting environments in schools/services compared to those who are members only;

2) Determine if children attending K-GFYL award schools/services have higher levels of healthy eating and physical activity-related behaviors compared to those who are members only;

3) Examine the barriers to implementing and achieving the K-GFYL award; and

4) Determine the economic cost of implementing K-GFYL in primary schools

Parent surveys will capture information about the home environment and child dietary and physical activity-related behaviors. Environmental questionnaires in early childhood settings and schools will capture information on the physical activity and nutrition environment and current health promotion activities. Lunchbox surveys and a set of open-ended questions for kindergarten parents will provide additional data. Resource use associated with the intervention activities will be collected from primary schools for cost analysis.

**Discussion:**

The K-GFYL award program is a community-wide intervention that requires a comprehensive, multi-level evaluation. The evaluation design is constrained by the lack of a non-K-GFYL control group, short time frames and delayed funding of this large scale evaluation across all intervention settings. However, despite this, the evaluation will generate valuable evidence about the utility of a community-wide environmental approach to preventing childhood obesity which will inform future public health policies and health promotion programs internationally.

**Trial Registration:**

ACTRN12609001075279

## Background

Currently, there is only limited evidence available about effective strategies to prevent childhood obesity. However community-based approaches to prevent childhood obesity that are multi-sector and multi-strategy show promise as being effective and also have the potential to be equitable, sustainable and cost-effective [1-8]. Schools, preschools and child care settings have all been identified as important settings for population-based obesity prevention efforts given their important role in promoting healthy eating and physical activity for children [9-11].

To date, settings-based child obesity prevention interventions have primarily been conducted in schools [1]. However, the socio-ecological framework identifies the multi-level influences on individual behaviors and recognizes that culture and ethos of the settings, organizational policies, practices and regulations, and engagement with the wider community are all important factors [12]. Kids - 'Go for your life' (K-GFYL) is a settings-based health promotion intervention that aims to reduce the risk of childhood obesity by using an award-based program to improve the socio-cultural, policy, and physical environments related to healthy eating and physical activity across the community [13].

### Kids 'Go for your life' Award Program

The K-GFYL intervention is being implemented in a range of children's settings, including primary (elementary) schools (children aged five to twelve years), pre-school (also known as kindergarten; for children aged three to five years), and the early childhood services family day care (FDC, a home-based child care service for children from birth to twelve years) and long day care (LDC, centre-based care for children aged from birth to five years). The K-GFYL program includes support and professional development for staff within those settings to make policy and practice changes that promote healthy eating and physical activity for children and their families [13]. The key obesity-related behaviors targeted are: increasing fruit, vegetable and water consumption; reducing consumption of foods high in fat, salt and sugar and sweet drinks; increasing participation in physical activity; reducing sedentary behavior (such as screen time); and increasing active transport [13]. The intervention was designed within a Health Promoting Schools (HPS) framework [14]; which requires a whole of school/service approach to health promotion. K-GFYL is an award-based program and membership is open to all primary and pre-schools, and early childhood services across the state of Victoria, Australia. Once members, the schools and services are supported to implement the program by a state-wide coordination team, a local government coordinator (available in 10 of the 79 local government areas in Victoria) and local community members of the Kids - 'Go for your life' Health Professionals' network. Once the school or service deems it has fully implemented the program and achieved all of the policy and practice requirements, they apply to become 'awarded' as a Kids - 'Go for your life' school or service. The application is reviewed and assessed by the state-wide coordination team and the award conferred if all of the appropriate criteria are met. From that time, they are referred to as a K-GFYL 'awarded' school or service. It is hypothesized that reaching award status increases children's physical activity and healthy eating behaviors through the creation of health promoting environments, capacity-building and community engagement (see Figure 1).

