**Figure 1 F1:**
[figure not shown]
**Kids-Go for your life program logic model**.

This paper describes the design of the evaluation of the K-GFYL intervention. Specifically the evaluation aims to:

1) Determine if K-GFYL award status is associated with more health promoting environments in schools/services compared to those who are members only;

2) Determine if children attending K-GFYL awarded schools/services have higher levels of healthy eating and physical activity-related behaviors compared to those who are members only;

3) Examine the barriers to implementing and achieving the K-GFYL award; and

4) Determine the economic cost of implementing K-GFYL in primary schools

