	School/service policy that includes a fruit break
	Information is provided to parents about healthy lunches and snacks
	Special days to promote fruit and vegetables such as: Free Fruit Fridays, nude food days (e.g. no packaged snacks), apple slinky days
	Students/children are involved in activities to grow and cook food
	Staff role modeling healthy eating and drinking practices
	Establishing links with local fruit and vegetable retailers
	Food is not used as a reward, incentive or for comfort
Unhealthy food and drinks	The school/service policy restricts unhealthy and promotes healthy foods and drinks
	The food service provides foods consistent with healthy eating guidelines and government policy
	Fundraising is consistent with healthy eating guidelines and policies
Physical Activity	Professional development opportunities for staff
	Established partnerships with local community and physical activity organizations^1^
	Structured and free active play sessions are planned on a daily basis
	Children have at least 30 minutes of structured active play and at least 60 minutes (and up to several hours) of unstructured play during their care session^2^
	Structural equipment (e.g. sandpit, fixed play equipment) is available for all students
	Classroom programs encourage physical activity during break time for all students^1^
	Staff role model being physically active
	Physical activity/active play policies are implemented
	Restrictions on screen-based activities (e.g. TV, DVDs, computers)
	Parents are provided with information about screen time recommendations for children and children's physical activity
Safe and Active	Promotion of walking/riding to school or other places ≥once/term^1^
Transport	Available bike storage for student and staff
	Child cyclist and pedestrian safety program
	Traffic calming measures outside the school/service
Curriculum and Policy	Teaching focused on healthy eating and physical activity, is incorporated in to the school curriculum plan^1^
	Whole school/service approach to healthy eating and physical activity
Families and School Community	Parents/carers are provided with information about the healthy eating and physical activity policy requirements and/or copies of the policies
	Information sessions/workshops for parents on healthy eating and physical activity

^1^Activities related to primary school settings only; ^2^Activities related to care settings only

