**Table 2 T2:** Overview of the evaluation design and instruments incorporating the socio-ecological framework [13]

Level of change	Description	Instrument	Participants	Setting
Environment/Policy	Policies, advocacy, environments, structures	Environment assessment Policy assessment	Settings staff	All
Intrapersonal	Individual characteristics/behaviours	Lunch Box Survey	Staff report of children's lunchbox content	PreS, FDC
		Child Health Questionnaire	Parents/guardians	PS
Community	Shared identities, experiences and resources for health	Qualitative data	Parents/guardians	PreS, PS

PreS: Preschools; FDC: Family Day Care; PS: Primary school;

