#### Policy analysis

Two policy checklists were developed for this evaluation based on our existing knowledge of school and service nutrition and physical activity policies and current evidence about important policy elements to promote nutrition and physical activity in children's settings [21-23]. The checklists have been piloted with a random sample of schools and services to ensure they extract the information required consistently across policies. After some refinement of wording, these checklists have been finalized (below) and will be used by trained research staff to determine the elements contained in the nutrition and physical activity policies. Research staff will also provide a rating (very poor, poor, good, very good) of 1) the structure and layout; and 2) readability and ease of understanding (simple and clear) of each policy.

Policy elements for nutrition/food-related policies:

1. Limit or restrict foods and drinks available through the food service (internal/external)

2. Ensure the food service menu meets government guidelines for healthy eating or nutritional quality

3. Ensure the availability of water for students/children

4. Restricting students' access to stores and food outlets, schools only

5. Restricting vending machines on the premises, schools only

6. Restricting foods associated with fundraising

7. Restricting foods associated with special events (e.g. birthdays, functions)

8. Setting aside adequate time for children to eat lunch/snacks

9. Promoting or restricting the types of foods that may be brought from home

10. Teaching that is focused on food and nutrition in the curriculum

11. Distribution of information to parents about healthy food and eating

12. Staff acting as role models in the area of healthy eating

13. Encouraging children to adopt healthy eating behaviors

14. Operating the food service on a not-for-profit basis

15. Foods are not used as rewards or punishment

16. Designated fruit/vegetable breaks

17. Promoting children's participation in growing, preparing and/or cooking food

18. Importance of healthy eating on learning outcomes (eg reduced absences, better behavior), schools only

19. Engaging with allied health professionals to implement health promotion activities

20. Providing professional development for staff regarding healthy eating

Policy elements for physical activity-related policies:

1. Providing access to play equipment out of class/session time

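### For items that are award criteria, part of the Aim 1 difference between awarded and member settings is built in by selection, so these items should be marked and reported separately

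*Protocol article*

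**What the plan says.** All of the following is in the protocol article.

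- **How a setting becomes awarded** (Kids 'Go for your life' Award Program). The setting judges itself first: "Once the school or service deems it has fully implemented the program and achieved all of the policy and practice requirements", it applies. Then an assessment follows: "The application is reviewed and assessed by the state-wide coordination team and the award conferred if all of the appropriate criteria are met".
- **What Aim 1 asks** (aims listed after Figure 1): "Determine if K-GFYL award status is associated with more health promoting environments in schools/services compared to those who are members only".
- **What is measured** (Table 2, environment/policy level): "Policies, advocacy, environments, structures". The instruments are the School Environment Questionnaire, its early-childhood counterparts, and checklists of 20 nutrition and 16 physical activity policy elements.
- **Who is compared** (Sampling). There are 30 member, 30 newly awarded and 20 longer-term awarded primary schools. School members must have joined less than 3 months earlier, a restriction chosen to widen the contrast. For preschools and long day care there are 20 member and 30 awarded.
- **How** (Data Analysis). Environmental data from primary schools, preschools and long day care are compared with chi-squared, Fisher's exact, t or Kruskal-Wallis tests, chosen by data type and distribution. The text does not distinguish items that are award criteria from items that are not.

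**The concern.** The exposure is a certificate that stated policies and practices are in place. The outcome is a survey of policies and practices. Where an item belongs to both, awarded settings have it because a setting without it could not have been awarded. A difference on such an item would appear even if the program changed nothing and settings that already complied simply applied.

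The risk is one of interpretation. A significant difference on a criterion item shows that the award assessment works and that compliance has lasted until the survey. It does not show that award status goes with a better environment beyond what the award requires. The limitations that the article lists (no control group outside the program, late and limited funding, short time frame, no local monitoring data) do not include this overlap, yet the Discussion expects the results to inform policy.

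**Working it through.** **1. Overlap, side by side.** The award criteria are not printed. Table 1, which lists program activities, is the nearest available text. Three of its nutrition entries refer explicitly to policy content and have a counterpart in the nutrition checklist:

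| Table 1 | Nutrition policy checklist |
|---|---|
| "School/service policy that includes a fruit break" | Element 16: "Designated fruit/vegetable breaks" |
| Drinking-water access written into policy | Element 3, availability of water |
| Policy restricting unhealthy food and drink | Element 1 (food service) or 9 (food from home) |

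Seven more elements have a Table 1 counterpart that is worded as a practice: 2 (food service guidelines), 6 (fundraising), 10 (curriculum), 11 (parent information), 12 (staff role modelling), 15 (food as reward) and 17 (growing and cooking). The checklist codes what a written policy contains, so carrying out the practice does not place it in the policy. These seven are possible overlaps, not shown ones. The environment questionnaires also ask about practices and program activities, but their items are not printed.

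**2. Built-in difference.** Let m be the proportion of members that have a criterion item, and c the proportion of awarded settings that still have it at the survey. With no program effect, the difference is c − m. At the time of award c = 100%. Both m and later c are assumptions here:

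- m = 70%, c = 100%: 30 points
- m = 70%, c = 95%: 25 points
- m = 90%, c = 95%: 5 points

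**3. The article's own figure.** For 20 v 30 settings it states a detectable difference of 40 percentage points with 80% power at 0.05 (two-sided assumed). Take 30% v 70%:

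- pooled proportion = (20 × 0.3 + 30 × 0.7)/50 = 0.54
- null SE = √[0.54 × 0.46 × (1/20 + 1/30)] = 0.1439
- alternative SE = √(0.21/20 + 0.21/30) = 0.1323
- z = (0.40 − 1.96 × 0.1439)/0.1323 = 0.89, so power is 81.4%

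The figure reproduces. No number in the article is wrong on this point.

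**4. Chance of a significant Fisher test on a criterion item with no program effect.** If c = 100%, only members can lack the item. With k members lacking it, p = C(20,k)/C(50,k) for 20 v 30:

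- k = 3: 1140/19600 = 0.058
- k = 4: 4845/230300 = 0.021

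So four or more members must lack the item. For 30 v 50 (taking both awarded school groups together, an assumption), k = 3 gives 4060/82160 = 0.049, so three are enough. The probabilities are then binomial tails. For example, at m = 70% and 20 v 30, P(Bin(20, 0.3) ≥ 4) = 89.3%. The c = 95% columns come from full enumeration of the two-sided Fisher test.

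| m | 20 v 30, c = 100% | 20 v 30, c = 95% | 30 v 50, c = 100% | 30 v 50, c = 95% |
|---|---|---|---|---|
| 50% | 99.9% | 96.3% | >99.9% | 99.8% |
| 60% | 98.4% | 86.3% | >99.9% | 97.4% |
| 70% | 89.3% | 64.1% | 99.8% | 84.8% |
| 80% | 58.9% | 30.8% | 95.6% | 50.3% |
| 90% | 13.3% | 4.6% | 58.9% | 10.7% |

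The effect ranges from near certainty to nothing, depending on two quantities that the article does not give.

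**The case against.** The strongest reply is that the comparison is not empty. The award starts from the setting's own judgement and an assessed application, whereas the evaluation relies on trained staff who code the policies and, in schools, interview staff. Whether the award matches what is found later is a fair question, and Aim 1 claims only an association. Much of what is measured is not shown to be an award matter, such as staff knowledge, skills and attitudes, or the layout and readability of policies. The newly v longer-term awarded school groups already address sustainability. A condensed article may also leave the grouping of items to a fuller document.

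Most of this stands, and it limits the point to criterion items. It does not remove the point, because the award rule, the aim and the overlapping content are all stated in the article, and how to read differences on such items is not.

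Three stronger readings are tempting but unsupported:

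- **Half of the nutrition checklist is fixed by the award.** A reader can match 10 of the 20 elements to Table 1. But Table 1 lists activities, not criteria, and only about three of the matches are explicit about policy content.
- **A pooled score mixes criterion and other items.** The article describes no composite score.
- **Aim 1 is close to certain to be positive, and so uninterpretable.** That needs low member prevalence and little lapse. Neither is documented, and the table above shows how quickly the result weakens without them.

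**Conclusion.** The point holds in a limited form. For items that are award criteria, part of the awarded v member difference is built in by selection at the time of award. For schools, restricting members to recent joiners is likely to widen the contrast. The size cannot be stated from the article. With all awarded settings compliant, the chance of a significant result with no program effect runs from 13% to 99.9% for 20 v 30 settings as member prevalence goes from 90% down to 50%. With 95% compliance it runs from 5% to 96%. These figures assume independent settings, a two-sided 0.05 level and prevalences chosen for illustration.

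Non-criterion items, the newly v longer-term awarded comparison and the child behaviors in Aim 2 are not fixed by the award definition. This is a worthwhile and inexpensive improvement to what Aim 1 can conclude, not a flaw that invalidates it.

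**What to change.** - Before analysis, use the award application form to mark every questionnaire and policy-checklist item as award criterion or not.
- Report the two sets separately. The planned tests can stay as they are.
- Read criterion items as fidelity and, in schools, by newly v longer-term awarded group, as maintenance. Give the percentage of each awarded group that still meets them.
- Rest any claim that award status goes with a more health-promoting environment, beyond what the award requires, on the non-criterion items.
- Add the overlap to the stated limitations.

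This needs no new data. It costs a short item-mapping exercise and leaves fewer items behind the claim that goes beyond the award requirements.

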**Figure 1 F1:**
[figure not shown]
**Kids-Go for your life program logic model**.

This paper describes the design of the evaluation of the K-GFYL intervention. Specifically the evaluation aims to:

1) Determine if K-GFYL award status is associated with more health promoting environments in schools/services compared to those who are members only;

2) Determine if children attending K-GFYL awarded schools/services have higher levels of healthy eating and physical activity-related behaviors compared to those who are members only;

3) Examine the barriers to implementing and achieving the K-GFYL award; and

4) Determine the economic cost of implementing K-GFYL in primary schools

## Methods/Design

### Evaluation design

When determining the appropriate evaluation design, the research team considered a number of contextual and limiting factors. These included 1) the implementation of the intervention program across the entire State and current high-level recruitment drive; 2) the funding of this evaluation more than 12 months after state-wide implementation began; 3) the requirement for the evaluation data to be available in a short time frame (all data was to be collected within one school term of 12 weeks); and 4) the limited evaluation funding for this large-scale impact and outcome evaluation in all of the settings targeted by the intervention. Taking these factors and the study aims into consideration, a mixed method, cross sectional evaluation design was deemed the most appropriate to determine differences in impact and outcome measures between those settings/services that were K-GFYL members only and those that were K-GFYL awarded. In the school setting, there will be two groups of awarded schools: newly awarded (<12 months) and longer term awarded (≥12 months), to enable an examination of the sustainability of program impacts after the award is conferred.

The K-GFYL intervention design, implementation strategies and materials were also carefully reviewed to determine the best evaluation methods given the constraints already mentioned. A summary of the main intervention activities implemented is provided in Table 1. Consistent with the intervention design, the evaluation design is guided by the socio-ecological framework [15] and accepted best practice for the evaluation of health promotion projects of this kind [16] (see Table 2). The evaluation was therefore also multi-level and the instruments are outlined in Table 2. The evaluation approach varies across settings due to the nature of the setting, data collection costs and accessibility to the setting/service and participants.

**Table 1 T1:** K-GFYL health promotion activities implemented in settings

K-GFYL Program area	Health promotion activity
Water and sweet drinks	Children have access to water throughout the day (water bottles, jugs and fountains)
	Sweet drinks are restricted or not allowed
	Having access to drinking water is reflected in school/service policy
Fruit and Vegetables	Defined periods of time when students/children are encouraged to eat fruit and vegetables only (e.g. Fruit & Veg play lunch, fruit break)
	School/service policy that includes a fruit break
	Information is provided to parents about healthy lunches and snacks
	Special days to promote fruit and vegetables such as: Free Fruit Fridays, nude food days (e.g. no packaged snacks), apple slinky days
	Students/children are involved in activities to grow and cook food
	Staff role modeling healthy eating and drinking practices
	Establishing links with local fruit and vegetable retailers
	Food is not used as a reward, incentive or for comfort
Unhealthy food and drinks	The school/service policy restricts unhealthy and promotes healthy foods and drinks
	The food service provides foods consistent with healthy eating guidelines and government policy
	Fundraising is consistent with healthy eating guidelines and policies
Physical Activity	Professional development opportunities for staff
	Established partnerships with local community and physical activity organizations^1^
	Structured and free active play sessions are planned on a daily basis
	Children have at least 30 minutes of structured active play and at least 60 minutes (and up to several hours) of unstructured play during their care session^2^
	Structural equipment (e.g. sandpit, fixed play equipment) is available for all students
	Classroom programs encourage physical activity during break time for all students^1^
	Staff role model being physically active
	Physical activity/active play policies are implemented
	Restrictions on screen-based activities (e.g. TV, DVDs, computers)
	Parents are provided with information about screen time recommendations for children and children's physical activity
Safe and Active	Promotion of walking/riding to school or other places ≥once/term^1^
Transport	Available bike storage for student and staff
	Child cyclist and pedestrian safety program
	Traffic calming measures outside the school/service
Curriculum and Policy	Teaching focused on healthy eating and physical activity, is incorporated in to the school curriculum plan^1^
	Whole school/service approach to healthy eating and physical activity
Families and School Community	Parents/carers are provided with information about the healthy eating and physical activity policy requirements and/or copies of the policies
	Information sessions/workshops for parents on healthy eating and physical activity

^1^Activities related to primary school settings only; ^2^Activities related to care settings only

**Table 2 T2:** Overview of the evaluation design and instruments incorporating the socio-ecological framework [13]

Level of change	Description	Instrument	Participants	Setting
Environment/Policy	Policies, advocacy, environments, structures	Environment assessment Policy assessment	Settings staff	All
Intrapersonal	Individual characteristics/behaviours	Lunch Box Survey	Staff report of children's lunchbox content	PreS, FDC
		Child Health Questionnaire	Parents/guardians	PS
Community	Shared identities, experiences and resources for health	Qualitative data	Parents/guardians	PreS, PS

PreS: Preschools; FDC: Family Day Care; PS: Primary school;

